**Methods/design:**

The effectiveness of a nurse-led intervention with the DT will be tested in a non-blinded randomized controlled trial. Patients treated with curative intent for breast cancer will be recruited from the Radboud University Medical Center. The intervention consists of the DT together with discussion of the results with the patient by a trained oncology nurse added to the usual care. Patients will be randomly allocated (1:1) to either receive usual care or the usual care plus the intervention. Primary outcome measure is global quality of life measured with the EORTC QLQ-C30. The functional and symptom scales of the EORTC QLQ-C30 and BR23, Hospital Anxiety and Depression Scale, Impact of Event Scale, Illness Cognition Questionnaire and DT (baseline and final measurement only) will be used to measure secondary outcomes. Questionnaires are obtained in both arms at baseline, after completion of each type of cancer treatment modality and during follow up, with a three and six months’ interval during the first and second year respectively.

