The following steps will be made for each screening moment with the DT:The patient will receive an e-mail or mail about the appointment with the trained oncology nurse, which will take place in combination with regular visits in the outpatient clinic.The patient will fill out out the DT in the outpatient clinic a few minutes before the appointment.The trained oncology nurse will discuss the DT with the patient before or after the visit with the attending healthcare professional. The nurse will ask on which problems the DT score is based and the mentioned problems on the problem list will be discussed. If the patient reports a lot of problems, the nurse will ask the patient to prioritize the problems indicated. At the end, the nurse will ask if the patient would like to be referred to a professional.Time allocated to these meetings will last between 5 – 30 min, depending on the severity of the distress and the nature of the problems.If the patient reports a DT score of <5 the trained oncology nurse will inquire whether the patient is sufficiently in control of her situation. The low distress score and the issues marked on the problem list are discussed briefly. At a score ≥ 5 on the DT, an extensive exploratory conversation between the nurse and the patient will take place. The outcome of this conversation will be discussed in a psychosocial Multi Disciplinary Team (MDT). The MDT has been established to discuss all patients of the intervention group with a score of ≥ 5 on the DT and to discuss patients who personally request additional support. The participants of the MDT are the attending healthcare professional and/or oncologist, the trained oncology nurse, a social worker and clinical psychologists. During the MDT a treatment plan is composed when needed. The nurse will propose this plan to the patient by phone.

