### Measuring time-points

The baseline measurement will take place preferably before breast surgery or start of the neo-adjuvant chemotherapy. During the first year of treatment the assessments will take place at the end of each treatment modality. In the second and third year, the follow-up visits will be in line with the recommendations of the Dutch Breast Cancer guideline [32]. This means that data will be collected approximately every 3 months during the first and every 6 months in the second year after the completion of adjuvant treatment (except for trastuzumab or hormonal therapy). This will result in a total of 8 – 10 measurements, depending on the number of adjuvant therapies (see Fig. 1). In order to monitor the effects of treatment on the patients’ well-being in both the short- and long-term, patients will be followed for two years after completion of the primary (adjuvant) treatment.

At all measuring time-points both groups will receive questionnaires. The DT is included for both groups at baseline and at the end of the study. At those time-points the results will not be discussed with the patients. Approximately two days before the regular visit to the attending healthcare professional, the patient will be asked to fill out the questionnaire electronically (Radquest software, department of Medical Psychology) or on paper in the hospital or at home. It takes 10–30 min to fill out the questionnaires. Additionally, a diary will be provided to the patient in which the consumed care and work absence has to be noted and recorded. At the moment the patient hands in the diary, a new one is provided by mail or personally. In case of non-response, a reminder will be send within 2 weeks by e-mail or mail.

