#### Secondary outcomes

The secondary outcomes will be: breast cancer related quality of life, anxiety, depression, emotional distress, coping, illness cognitions and distress (Table 1).

**Table 1 Tab1:** Measurements and time points of the nurse intervention project

Questionnaires	Target	T0	T1-T8	T9	Response format
Demographic & medical characteristics	Descriptive of the population	X	X	X	Multiple answers
EORTC QLQ-C30	Functional scales: physical, role, emotional, social, and cognitive functioning (15 items)	X	X	X	4 point Likert scale Range 15–60
	Symptom scales: fatigue, pain, nausea/vomiting (7 items)	X	X	X	Range 7–28
	Single symptom items (6 items)	X	X	X	Range 6–24
	Global Health and global quality of life* (2 items)	X	X	X	7 point linear analogue scale Range 2–14
EORTC QLQ- BR23	Functional scales: body image, sexual functioning, sexual enjoyment, future perspective (8 items)	X	X	X	4 point Likert scale Range 8–32
	Symptoms scales: arm symptoms, breast symptoms, systemic therapy side effects, upset by hair loss (15 items)	X	X	X	Range 15-60
DT	General distress	X	X^1^	X	11 point visual analogue Scale: range 0–10
	Problem list (47 items)	X	X^1^	X	Yes/no
	Question: wish for referral (1 item)	X	X^1^	X	Yes/no/maybe
HADS	Emotional distress (14 items) Subscales: Anxiety (7 items) Depression (7 items)	X	X	X	4 point Likert scale Range 0–42 (total scale) Range 0–21 Range 0-21
IES	Coping with the cancer (15 items) Subscales: Intrusion (7 items) Avoidance (8 items)	X	X	X	4 point scale Range 0–75 (total score) Range 0–35 Range 0-40
ICQ	Illness perceptions (18 items) Subscales: Helplessness (6 items) Acceptance (6 items) Perceived benefits (6 items)	X	X	X	4 point Likert scale Range 6–24 Range 6–24 Range 6-24
Diary	Health care use and work absence		X	X	Yes/no, frequency and reason
EQ-6D	Quality of life in relation to economic evaluations (1 item)	X	X	X	Visual Analogue Scale: range 0–100
	Dimensions: mobility, self-care, usual activities, pain/discomfort, anxiety/depression and cognition (6 items)	X	X	X	Range 1–3 for each dimension.

*primary outcome

^1^only in the intervention group

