*Abbreviations*: *T0* baseline measurement, *T1-T3* measurement after each treatment and T4-T8 follow up, *T9* final measure, *EORTC QLQ-C30* European organization for research and treatment of cancer, quality of life questionnaire, *QLQ-BR23* quality of life- breast cancer, *DT* distress thermometer, *HADS* hospital anxiety and depression scale, *IES* impact of event scale, *ICQ* illness cognition questionnaire, *EQ-6D* euroQol-6D

Functional and symptom scales of the EORTC QLQ C30 will be used to assess the other dimensions of quality of life (see Table 1). Higher scores on the global and function scales implies good quality of life. On the symptom scales, low scores indicates less intense symptoms hence higher quality of life [33-35].

*Breast cancer related quality of life* will be assessed with the breast cancer related questionnaire EORTC- BR23 which consists of 23 questions and complements the C30 [36].

*Anxiety, depression* and *emotional distress* will be measured with the Hospital Anxiety and Depression Scale (HADS). The HADS has two subscales (anxiety and depression) and a total score of emotional distress. The questionnaire consists of 14 questions with scores ranging from 0 (not at all) to 3 (very much) [37–39].

The presence of *coping problems* will be measured with Impact of Event Scale (IES). This questionnaire provides an inventory of the effects of a shocking event and focuses on the person’s feelings and thoughts over the previous seven days. The IES has two subscales: intrusion and avoidance. The scores range from ‘not at all’, ‘rarely’, ‘sometimes’ and ‘often’[40].

To identify the role of *illness cognitions* in relation to the treatment effectiveness we will use the Illness Cognition Questionnaire (ICQ). There are three subscales: helplessness, acceptance and perceived benefits. The scores range from 1 (none) to 4 (entirely) [41].

*Distress* will also be measured with the DT at baseline and final measurement for both groups (see Fig. 1) [14].

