### Statistical analysis

The primary analysis is the comparison of the primary outcome global quality of life subscale of the EORTC QLQ-C30 as measured at the end of the research period analyzed by ANCOVA, i.e., an adjustment for baseline will be included. The secondary analysis of the primary outcome is a repeated measurements analysis of the sequence of the repeated measurements in order to compare the trends between the two groups (mixed model for repeated measurements). Similar analysis will be carried out on the secondary outcomes. Subgroup analysis will be performed on demographic and treatment characteristics.

Missing data will be analyzed with the last observation carried forward method for the ANCOVA and a sensitivity analysis assuming missing data to be missing-at-random will be performed using a mixed model for repeated measurements. Patients who have died, had recurrence or metastasis of the breast cancer, or were diagnosed with another malignancy during the study will be considered to have dropped out of the study from that event onwards.

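### The blanket analysis rule for secondary outcomes does not fit the Distress Thermometer, which controls complete only at T0 and T9

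*Protocol article*

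**What the plan says.** The Statistical analysis section sets three rules for the primary outcome:

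- ANCOVA at the end of the study, adjusted for baseline.
- A "repeated measurements analysis of the sequence of the repeated measurements in order to compare the trends between the two groups", by mixed model.
- For missing values: "Missing data will be analyzed with the last observation carried forward method for the ANCOVA", with the mixed model under missing-at-random as sensitivity analysis.

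It then adds "Similar analysis will be carried out on the secondary outcomes". No outcome is exempted.

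Distress measured by the DT is a listed secondary outcome. Its schedule appears in four places:

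- Abstract, Methods/design: "DT (baseline and final measurement only) will be used to measure secondary outcomes".
- Measuring time-points: "The DT is included for both groups at baseline and at the end of the study".
- Secondary outcomes, text: distress "will also be measured with the DT at baseline and final measurement for both groups".
- Secondary outcomes, Table 1: the DT is marked at T0, T1–T8 and T9, and a footnote to T1–T8 reads "only in the intervention group".

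The Intervention section shows what the T1–T8 scores are: "The patient will fill out out the DT in the outpatient clinic a few minutes before the appointment". They belong to the nurse contact itself.

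**The concern.** The rule was written for questionnaires that both arms complete at every visit. The DT is the one listed outcome for which that is not so, and two things follow.

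First, the trend comparison has nothing to compare at T1–T8, because the control arm has no scores there. The mixed model is also the stated check on LOCF, so for the DT that check would have interim data in one arm only.

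Second, the words last observation mean different things in the two arms. A control drop-out's last DT score is always T0, close to diagnosis. An intervention drop-out's last score can be from any visit up to T8. Carried to T9, these give a between-arm difference even without a treatment effect, unless average distress stays constant.

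Drop-out is expected. The power section allows for up to 15 %, and the Statistical analysis section also counts death, recurrence, metastasis and a new malignancy as drop-out from the event onwards. The DT is the outcome closest to what the intervention screens for, and the Discussion looks to the secondary outcomes for evidence that distress has fallen.

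**Working it through.** **The plan's own figures.** The plan gives no figure for the DT. It gives 84 patients per group, at most 15 % drop-out and 193 in total: 168 × 1.15 = 193.2, which reproduces 193. Half of that is 96.5, so 97 per arm is used below.

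**Assumptions, because the documents give no DT data.** SD 2.5, within-patient correlation 0.5, two-sided alpha 0.05, drop-out of 15 % in each arm and unrelated to the scores, no treatment effect, and the mean trajectories named below.

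**Trend comparison.** Set Table 1 beside the trend rule: control scores exist at T0 and T9, intervention scores at T0 to T9. Only the T0-to-T9 change is comparable between arms. This holds on any reading of the text.

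**LOCF if T1–T8 scores are used.** Under no effect,

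bias (intervention − control) = drop-out share × (mean score carried in the intervention arm − mean T0 score).

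Take a linear fall from 5 to 3 over T0–T9, a step of 2/9 = 0.222 per visit:

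- Early drop-out (first missed visit T1–T4, last score T0–T3): mean fall 1.5 × 0.222 = 0.333; bias −0.15 × 0.333 = −0.05.
- Uniform (last score T0–T8): 4 × 0.222 = 0.889; bias −0.13.
- Late (first missed visit T6–T9, last score T5–T8): 6.5 × 0.222 = 1.444; bias −0.22.

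The other trajectories follow the same formula. Type I error comes from simulated ANCOVA, 3,000 runs per scenario (Monte Carlo standard error at 5 %: √(0.05 × 0.95/3000) = 0.4 percentage points). Negative bias favours the intervention.

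| Assumed mean DT | Bias: early / uniform / late drop-out | Type I error, same order |
|---|---|---|
| Linear fall 5 to 3 | −0.05 / −0.13 / −0.22 | 4.5 % / 7.1 % / 10.4 % |
| Front-loaded fall 5 to 3 | −0.09 / −0.18 / −0.26 | 6.2 % / 8.5 % / 14.0 % |
| Flat at 4 | 0 / 0 / 0 | 5.1 % / 5.1 % / 4.6 % |
| 5, peak 6.5 during treatment, then 3 | +0.13 / −0.05 / −0.23 | 7.0 % / 5.1 % / 11.1 % |
| Linear rise 3 to 5 | +0.05 / +0.13 / +0.22 | 6.0 % / 7.3 % / 11.0 % |

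**LOCF if only T0 and T9 count.** Every drop-out in either arm carries T0. The simulated null bias is −0.013 to +0.007 and the type I error 4.4–5.2 % over the same trajectories, so the asymmetry is gone. Two defects remain:

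- With a 2-point fall, each arm's T9 mean is overstated by 0.15 × 2 = 0.30. If drop-out differs between arms, the bias is (intervention share − control share) × 2, or 0.02 DT points per percentage point of difference.
- Drop-outs contribute a pre-treatment score, so a true T9 difference δ is estimated as (1 − 0.15)δ = 0.85δ.

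**The case against.** The strongest objection is that the outcome is already defined as T0 and T9. The Abstract and the Secondary outcomes text say so, and the Intervention section shows that the T1–T8 scores are part of the treatment. On that definition LOCF treats both arms alike. The rule also speaks of a similar analysis, not an identical one, and a condensed article may leave imputation detail to an analysis plan. Most of this stands, and it is why the asymmetry is put here as conditional. It does not remove the point: the analysis rule makes no exception, Table 1 lists the T1–T8 scores among the measurements, and a literal reading of last observation would use them. The trend comparison fails for the DT on either reading.

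A reader might also infer that LOCF favours the intervention by construction. The documents do not support that. The asymmetry is structural, but its direction depends on a DT trajectory that no section gives. The Discussion expects natural recovery of quality of life, which makes falling distress plausible, but T1–T3 follow treatment modalities, where distress could peak.

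A larger size is tempting too. With falls of 2 or 3 points, 0.15 × 2 = 0.30 and 0.15 × 3 = 0.45; against a standard error of 2.5 × √(2/96.5) = 0.36 these are shifts of 0.83 and 1.25 standard errors, and false-positive rates of about 13 % and 24 %. This needs every intervention drop-out to have shown the whole fall before leaving. With a 2-point fall and drop-out spread over visits, the simulated rates stop at 14 %.

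Finally, a mixed model is not useless here. It can still estimate the T9 contrast under missing-at-random; what it cannot deliver is the T1–T8 trend comparison.

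**Conclusion.** The point holds in limited form. The plan applies to the DT a trend comparison that its own schedule rules out, and a carry-forward rule that serves the DT badly on either reading: unequal between arms if the T1–T8 scores are used, or a diagnosis-time score standing in for a visit more than two years later if they are not.

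On the first reading, with 15 % drop-out, a 2-point fall and SD 2.5, the bias is about 0.05–0.26 DT points towards the intervention and the type I error about 4.5–14 %; the lower end is indistinguishable from the nominal 5 %. The bias is nil if distress is flat, and goes against the intervention if distress rises or peaks during treatment with early drop-out. These sizes rest on assumed DT means, SD, correlation and drop-out timing.

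It would be wrong to infer that the trial's main result is at risk. The primary outcome and the other secondary questionnaires are collected in both arms at every time point, the DT is not among the secondary outcomes that the power section calls most important, and the HADS measures emotional distress on the same schedule in both arms. Severity is minor to moderate.

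**What to change.** Add to the Statistical analysis section, directly after the sentence on secondary outcomes, that:

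- the DT is analysed from T0 and T9 only, identically in both arms, by ANCOVA or a two-time-point model under missing-at-random;
- any imputation of T9 uses only variables collected in both arms, such as the HADS and QLQ-C30 emotional functioning;
- the DT is exempt from LOCF and from the repeated-measures trend comparison;
- the intervention-arm T1–T8 DT scores are reported descriptively, as process data.

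The cost is a few lines of analysis text. No new data, visits or patients are needed, and the wording then agrees with how the Abstract and the Secondary outcomes section already define the outcome.

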## Discussion

This study will evaluate the effect of an oncology nurse-led DT intervention compared to usual care on improving the quality of life of patients who are treated for breast cancer with curative intent. The results will contribute to the actual knowledge and the current discussion about using the DT in daily oncology practice [25-27], as most previous studies were performed for validation of the DT. Even though Hollingworth et al. performed an RCT to measure the efficacy of the DT, they used the DT once [24]. In our study, we will offer a nurse-led DT intervention repeatedly in a period of more than two years, which makes our study unique and complementary to the existing literature. Despite a natural recovery of quality of life over time, we will expect additional improvement when using the DT systematically during a longer period. As a primary endpoint, we will use the EORTC QLQ-C30 global quality of life scale. In order to compensate for probable response shift, we will also inspect the secondary outcomes to measure distress reduction. Additionally, the results of this study will give us insight into the trajectories of distress and quality of life from diagnosis to 2-year follow up in the usual care group. The short- and long-term problems of patients with breast cancer will become apparent. Therefore, the outcome of our study may have impact on the future implementation of the DT both nationally and internationally. The strengths of our study are: (1) we will follow the guideline about distress management, (2) we will systematically assess and discuss the DT for approximately 2 years follow up, (3) we will discuss the DT results of all patients in the intervention group with high distress in a psychosocial MDT.

## Conclusion

In conclusion, the aim of our study is to determine the effectiveness of the systematic use of the DT and the subsequent discussion of the results with a trained oncology nurse compared with usual care on the quality of life of the patient with breast cancer. It is anticipated that the results of the study will have impact on the future implementation and standardization of the use of the DT as part of routine care. It is expected that the data collection will be completed early 2016.
